#### Reminder call

3.4.1

The purpose of a reminder call is to remind the patient about the time for taking immunosuppressive medications and periodic appointment. Medication reminder calls will be done once a day based on the type of immunosuppressive medications which are recorded in the patient profile. The IVRS will contact the patient's mobile number and remind them about taking their medication. In the absence of an answer, the system will call again 30 seconds later, and if she\he does not respond, it will send a text message containing the medication reminder.

The periodic appointment reminder calls will be done every 2 months based on the date of referral which is recorded in the patient's profile a day before their appointment. Moreover, on the day of appointment, patients will receive a reminder in the form of an SMS.

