### Sample size

3.6

According to the study by Garcia et al,^[35]^ an study effect size based on 90% power and data with a 2-tailed *α* = 0.05, in medication adherence between the control and intervention groups, was estimated to be 40 patients in each group. Considering the 50% prop up rate during the study, our goal is to employ 60 patients in each group.

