### Randomization

3.8

After reviewing the outpatient medical records of patients referred to the clinic, we first obtain their informed consent. Then participants will be stratified into different strata based on their respective date of transplantation. The first stratum will be included participants who have received a transplant between March 21, 2015 and March 20, 2017, and the second stratum will include recipients who have received a transplant between March 20, 2012 and March 20, 2015. In fact, the goal is to eliminate the effect of post-transplantation time in evaluating self-management patients. Then participants will be randomly assigned to the control or intervention group in each stratum. For generating the allocation sequence, we will be used computer-generated random numbers provided by www.randomization.com. Randomization sequence will be created by an independent researcher, who is not involved in the collection or intervention procedure. The allocation ratio of intervention: control is 1:1.

For each patient, a folded paper, containing the assignment group together with a unique identification number in the study, will be stored in a sealed envelope, such that the information will not be readable without opening the envelope. Sealed envelopes are arranged based on randomized sequences. The assistant researcher will collect the baseline questionnaire and assigns the patient to the relevant stratum. Subsequently, the assistant researcher contacts the researcher (responsible for registering the patient in the IVRS) and the researcher will assign the patient to 1 of the 2 intervention or control groups. If the participant is assigned to the intervention group, the researcher registers the participant in the IVRS based on baseline information.

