### Statistical analysis

3.12

For participants in the 2 groups, the intervention and control, medication adherence will be measured and documented based on the BASSIS self-report at baseline, 2, 4, and 6 months. For determining effect of each predictor variable and modifying the effect of confounding, we will use ordinary logistics regression and multinomial logistics regression models. To evaluate quantitative variables at different time points, if the variables have a Gaussian distribution, the repeated ANOVA measure, and otherwise the Friedman test, will be used. Cochrane test will be used to evaluate and compare medication adherence across different time points. *P*-values less than .05 will be considered as statistically significant. All statistical analyzes will be performed using the Statistical Package for the Social Sciences, version 23, IBM. The electronic data file is stored on secure data servers and its hard copy version will be stored in a locked file at MUMS.

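### The repeated-measures tests named for four assessments exclude any patient who misses one, while the sample-size section allows for losing roughly one third to one half of patients

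*Protocol article*

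**What the plan says.** The Outcomes measure section has primary and secondary outcomes assessed four times: at baseline and 2, 4 and 6 months later. Adherence by self-report is primary; transplant knowledge (K-TUT) and quality of life (SF-12) are among the secondary outcomes.

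The Statistical analysis section fixes the tests over time. For quantitative variables, "if the variables have a Gaussian distribution, the repeated ANOVA measure, and otherwise the Friedman test, will be used". For adherence it names a Cochrane test across the time points, which I read as Cochran's Q. It also names logistic and multinomial logistic regression, for the effects of predictors and for confounding.

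The Sample size section says the requirement "was estimated to be 40 patients in each group", and continues: "Considering the 50% prop up rate during the study, our goal is to employ 60 patients in each group".

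On contact with patients, the Participants section gives the interactive voice response system (IVRS) to the intervention arm only. The Reminder call section says "The periodic appointment reminder calls will be done every 2 months based on the date of referral", with a text message on the day itself. The same arm also gets daily medication reminders, daily educational calls and daily adherence questions. Under Medication adherence call, the researchers may remove a participant who misses more than two follow-up visits.

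**The concern.** The classical forms of repeated-measures ANOVA, Friedman's test and Cochran's Q work on a complete patient-by-time table. A patient with one empty cell is left out altogether, and the values that were observed go too. This is a consequence of the tests the article commits to, not a detail left for later.

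Two things make it matter here. First, the plan itself budgets for large losses, so the excluded share is not a few stray patients. Patients who miss only one or two visits need not be removed under the protocol's rule, yet they would still drop out of these tests.

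Second, who completes may depend on both arm and outcome. Appointment reminders go to one arm at the same two-month spacing as the assessments. The Introduction treats keeping appointments and taking immunosuppressants as parts of the same self-management behaviour. If reminders keep less adherent patients in follow-up in one arm, or daily calls tire them out, an arm comparison confined to completers no longer compares the groups as randomised.

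**Working it through.** **Inputs from the protocol.** 40 evaluable and 60 recruited per arm, the 50% rate, 90% power and two-sided 0.05 (Sample size); 1:1 allocation (Randomization); four assessments (Outcomes measure).

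**1. The plan's own figure.** 40 × (1 + 0.5) = 60, which reproduces the target. Dividing by the retained fraction gives 40 / (1 − 0.5) = 80, which does not. The wording "Considering the 50% prop up rate during the study" therefore has two readings:
- 50% drop-out: 60 × 0.5 = 30 completers and 30 excluded per arm (60 of 120 overall).
- 50% mark-up on 40: 40 completers and 20 excluded per arm, a loss of 1 − 40/60 = 33%.

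Visits missed by patients who stay in the study would add to either figure.

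**2. Data set aside.** Assume that loss accrues evenly to month 6.
- At 50% loss, 60, 50, 40 and 30 patients per arm are seen, 180 observations. Completers supply 30 × 4 = 120. The 60 discarded (one third) are 30 at baseline, 20 at month 2 and 10 at month 4.
- At 33% loss, 60, 53.3, 46.7 and 40 are seen, 200 observations. Completers supply 40 × 4 = 160. The 40 discarded (one fifth) are 20 at baseline, 13.3 at month 2 and 6.7 at month 4.

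So the share of observations lost is smaller than the share of patients lost.

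**3. Power with 30 per arm.** The article gives no rates or SD, so the effect behind 40 per arm is back-solved as a standardised difference: (1.960 + 1.282) × √(2/40) = 0.725. With 30 per arm, power is Φ(0.725 × √(30/2) − 1.960) = Φ(0.847), about 80% instead of 90%. For two proportions, with control adherence assumed between 20% and 60%, it is 79.7% to 79.9%. This is for a simple two-arm comparison. It reflects the attrition itself, and a model using earlier visits recovers only part of it.

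**4. How selection could act.** All values here are assumed. Let true adherence be p = 0.5 in both arms, with retention r_a among adherent and r_n among non-adherent patients. Adherence among completers is p·r_a / (p·r_a + (1 − p)·r_n). Differences are IVRS minus control.
- Both arms 0.6/0.4: 0.600 and 0.600, difference 0.
- Control 0.6/0.4, IVRS 0.5/0.5: 0.600 and 0.500, difference −10 points.
- Control 0.7/0.3, IVRS 0.5/0.5: 0.700 and 0.500, difference −20 points.
- Control 0.55/0.45, IVRS 0.6/0.3: 0.550 and 0.667, difference +12 points.

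These apply to any arm comparison of adherence restricted to completers. Cochran's Q and Friedman's test compare time points and do not estimate an arm difference.

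**The case against.** The strongest reply is that the arm comparison of adherence need not run through these tests at all. Of the methods named, only logistic regression can estimate an arm effect on binary adherence, and it does not by itself require all four visits. That stands: not every named analysis is complete-case, and the differences in step 4 are not estimates from the plan's adherence test. What remains is that the article assigns the regressions to predictors and confounding, and the comparison over time to the tests that need complete data. Repeated-measures ANOVA, the one named test over time that can compare arms, is still affected for K-TUT and SF-12.

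A reader might infer that half the sample is certain to be discarded. The documents do not support that: the 50% phrase is garbled, and 60 = 40 × 1.5 fits a 33% loss as well.

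A reader might also infer that completers are in fact selected differently by arm. The article gives no retention by arm and does not say that questionnaires are collected at the reminded appointments. This is a plausible risk, no more.

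It can also be said that imputation and sensitivity analyses belong in a full protocol or SAP. That is fair, and their absence from the article is not counted here. The point rests on the tests the article does name. One could run the repeated-measures analysis as a mixed model, but the text does not say so, and the Friedman alternative would still need complete data.

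**Conclusion.** The point holds in limited form. The three tests over time, in their classical form, would exclude about 20 to 30 of 60 patients per arm on the plan's own allowance. With even loss, that is about one fifth to one third of the observations collected. Intermittent missed visits would raise these figures; loss soon after baseline would lower the amount of follow-up data wasted.

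Arm-dependent selection is credible because contact and reminders differ by arm, but its size and direction are unknown and may be zero. The stronger conclusion, that the primary comparison is biased, is not supported: the article does not specify a completers-only estimate of the arm difference in adherence. The choice should be changed before analysis, since a better method needs no further data.

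**What to change.** Replace the three tests with models that use all observed visits of all randomised patients in their assigned arm. Include arm, visit, arm-by-visit interaction, the baseline value and the transplant-date stratum.
- **K-TUT and SF-12:** a linear mixed model.
- **BAASIS adherence:** a mixed logistic model, or GEE with weighting or with imputation that includes the 2- and 4-month values. Unweighted GEE on the available data would not be enough if loss depends on earlier adherence.

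Say that this is the longitudinal analysis, and what role the logistic regressions then have.

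The cost is revised wording and modest programming, with no extra patients or data. The downside is reliance on data being missing at random. If loss depends on current, unobserved adherence, as in the illustration, these models reduce the bias only as far as observed visits predict loss. A simple sensitivity analysis that assumes lower adherence among missing patients, varied by arm, would probe this and can sit in the SAP.

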Health education programs are aimed to improve outcomes, increase the benefits for the community, and, consequently, enhance public health.^[26]^ More specifically, the program logic model (PLM) helps to identify the measurable outcomes in the causal chain.^[27]^ PLM offers a framework to guide the content of e-health education programs, enabling the healthcare providers to more effectively define and measure objectives, empower patients, and improve patient care.^[28]^ The PLM will be used during the development and implementation phases of this study. According to the PLM, patient education results in proximal outcomes (eg, knowledge and compliance) and intermediate outcomes (eg, self-efficacy and QoL). As a long-term effect, patient education programs might decrease or eliminate the loss of productivity, increase community capacity, and increase the efficiency of health care resources. Since post-transplant management is a complex process and KT recipients have a lot to learn, inadequate patient knowledge can easily result in dire consequences (eg, decreased adherence to recommendations and organ rejection).^[29,30]^ We hypothesized that automatic IVRSs designed based on educational and theory-driven intervention which is acceptable to the individual patient would improve self-management in KT recipients who received IVRS compared to patients who only received usual care. Thus, we designed a randomized, 2 parallel groups controlled trial to evaluate the effect of an IVRS intervention on self-management outcomes (such as immunosuppressant medication adherence, transplant knowledge, and quality of life) among KT recipients.

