#### Study design

3.2.1

A randomized, 2 parallel groups, controlled trial in accordance with the Consolidated Standards of Reporting Trials guidelines^[33]^ was designed (Fig. 2). The protocol is reported in accordance with the Standard Protocol Items: Recommendations for Interventional Trials 2013 Statement.^[34]^

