### Outcomes measure

3.5

Study outcomes will be evaluated in accordance with Table 1. Primary and secondary outcomes are measured at baseline, and at 2-months, 4-months, and 6-months after baseline. For ethical reasons, if the intervention is found to be effective, all groups will have access to IVRS at the end of the intervention. Primary outcome will be immunosuppressive medication adherence that is evaluated based on a self-report in both groups during the follow-up period. The secondary outcomes include transplant knowledge, HRQoL, and rehospitalization rate.

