## Results

4

We have complete preliminary qualitative and expert opinion studies that provide educational content, profile information, and intervention design. Recruitment of participants has not been completed and results will be published in 2019. The IVRS is potentially useful to help KT recipients improve self-management outcomes. Using IVRS intervention will make significant differences between BAASIS, SF-12V2, K-TUT scores, when comparing these at baseline and at the end of study.

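### The only test expressly tied to the primary outcome compares visits, not the randomised arms, and no between-arm analysis of adherence is named

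*Protocol article*

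**What the plan says.** The aim is a comparison of arms. The Introduction hypothesises that the system "would improve self-management in KT recipients who received IVRS compared to patients who only received usual care". Section 3.2.1 describes "A randomized, 2 parallel groups, controlled trial", and section 3.8 adds: "The allocation ratio of intervention: control is 1:1". Section 3.6 bases the sample size on an effect "in medication adherence between the control and intervention groups".

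Section 3.5 sets the endpoint: "Primary outcome will be immunosuppressive medication adherence that is evaluated based on a self-report in both groups during the follow-up period". Section 3.10 makes it yes/no at each assessment, since any BAASIS answer other than never counts as non-adherent. Assessments are at baseline and at 2, 4 and 6 months.

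Section 3.12 assigns one test to this endpoint by name: "Cochrane test will be used to evaluate and compare medication adherence across different time points". It also says: "For determining effect of each predictor variable and modifying the effect of confounding, we will use ordinary logistics regression and multinomial logistics regression models". That sentence names no outcome, no arm term and no visit. The repeated-measures ANOVA and Friedman test in the same section are for quantitative variables.

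Section 4 describes the expected result as a change over time: "Using IVRS intervention will make significant differences between BAASIS, SF-12V2, K-TUT scores, when comparing these at baseline and at the end of study".

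**The concern.** The question posed and the test named for it do not match. A test across visits answers whether adherence moved during the study, whereas randomisation supports an answer to whether it moved differently under IVRS.

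Both arms complete the same adherence questionnaire four times while enrolled in a study about self-management, so a rise shared by both arms is plausible. If the named test is followed literally, such a rise could be reported as efficacy. A significant change in the IVRS arm beside a non-significant one under usual care is no safer, because that pattern is not a test of the difference between arms. The opposite error is also possible: if IVRS merely holds adherence steady while usual care declines, a test of change in the IVRS arm has nothing to find.

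**Working it through.** **1. Which test is meant.** Cochrane test is read here as Cochran's Q. This is an inference. It rests on a binary outcome, four repeated assessments, wording about time points, and a Friedman test (the counterpart for quantitative data) in the preceding sentence. A Cochran-Mantel-Haenszel test would compare groups across strata, which is not what the sentence describes.

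**2. What the test contains.** For k visits with adherent counts C_j, patient totals R_i and overall total N,

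Q = (k − 1)(k ΣC_j² − N²) / (kN − ΣR_i²), on k − 1 degrees of freedom.

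Here k = 4, giving 3 degrees of freedom. Arm appears nowhere in the formula.

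**3. The plan's own figure.** The 40 per group cannot be reproduced, because section 3.6 gives no rates or effect size. Solved backwards at 90% power and two-sided alpha 0.05, it corresponds to a standardised difference of (1.960 + 1.282) × √(2/40) = 0.725. For proportions, it corresponds to, for example, 50% versus about 83.5% (no continuity correction). These are differences between arms, which Q does not estimate.

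**4. A worked case (assumed rates).** Take 40 per arm. Adherence moves from 55% to 75% under IVRS and from 55% to 35% under usual care.
- IVRS counts: 22, 25, 27, 30.
- Usual care counts: 22, 19, 17, 14.
- Visit totals, both arms together: 44, 44, 44, 44, so N = 176.
- Numerator term: 4 × (4 × 44²) − 176² = 30,976 − 30,976 = 0, so Q = 0.
- Month 6 between arms: 30/40 versus 14/40, z = 0.40 / √(0.55 × 0.45 × 2/40) = 3.60.

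On all patients together, Q sees nothing where the arms differ by 40 percentage points.

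**5. Simulation with no treatment effect.** Assumptions: 40 per arm, latent-normal binary data, correlation 0.5 between visits, the same path in both arms, baseline adherence 50%.

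| Path in both arms | Q significant, IVRS arm | Q significant, IVRS arm only | Between-arm test, month 6 |
|---|---|---|---|
| To 65%, complete by month 2 | 36-37% | 23-24% | about 5% |
| To 65%, gradual | 26-27% | 19-20% | about 5% |
| To 70%, complete by month 2 | 60-62% | – | about 5% |
| To 70%, gradual | 47% | – | about 5% |
| To 60%, gradual | 14% | 12% | about 5% |

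With a steeper shared rise (40%, 60%, 65%, 70%), 40 or 60 per arm and correlation 0.3 or 0.6, Q on both arms together rejects in 98.6-100% of trials. Significance in the IVRS arm only occurs in 1.6-18%; it becomes less common as Q turns significant in both arms. The between-arm test rejects in 3.6-5.8%.

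**6. Simulation with a true effect.** If IVRS holds adherence at 70% while usual care falls from 70% to 40%, Q in the IVRS arm rejects in about 4-6% of trials, its false-positive rate. The between-arm test at month 6 detects the difference in 79-93%.

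**The case against.** The strongest reply is that section 3.12 does list a method able to compare the arms. Its opening sentence mentions the two groups and medication adherence, and logistic regression follows directly. Read in sequence, adherence is a natural outcome and arm a natural predictor. The article is condensed, and model terms are often left to an analysis plan. This stands in part: a reader might infer that the plan contains nothing capable of testing the hypothesis, and the text does not support that. What remains is that the regression is described as serving predictors and confounding, while the one test expressly attached to the primary outcome answers another question. That is a stated choice, not merely a detail left out.

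Four further inferences are tempting but unsupported.
- That the multinomial model is misapplied to yes/no adherence: section 3.12 does not assign it there, and section 3.10 defines a three-level quality-of-life classification that it would suit.
- That visits will be pooled as independent records, inflating type I error: no such analysis is stated, and a logistic model at one visit has no such problem.
- That regression to the mean would raise adherence: the eligibility criteria in section 3.3 do not select on adherence.
- That section 4 settles the intended inference: it states an expectation, not an analysis rule, and the Introduction and section 3.6 state the between-arm aim.

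It is also fair to say that the simulated percentages depend strongly on the assumed path. They illustrate the problem and do not forecast this trial.

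**Conclusion.** The point holds in this form: the only test section 3.12 expressly assigns to the primary outcome compares visits and has no group term, whereas the hypothesis, design and sample size concern IVRS versus usual care. The regression that could fill the gap is not given that task.

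The mismatch follows from the definition of the test and needs no assumed rates, only the reading of the test as Cochran's Q. Its size does need them. For a shared rise from 50% to 65%, 40 per arm and latent correlation 0.5, Q would suggest a change in the IVRS arm in about 26-37% of trials without any treatment effect, and in that arm only in about 19-24%. The lower ends belong to a gradual rise and the upper ends to one complete by month 2. Smaller or larger shared rises move these figures, as the table shows. The between-arm test keeps its 5% level throughout.

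This should be settled before analysis, because it decides whether the primary result can be read as an effect of IVRS.

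**What to change.** Name one between-arm primary analysis of BAASIS adherence in section 3.12. Either of these would do:
- a GEE or mixed logistic model over months 2, 4 and 6 with arm, visit, arm-by-visit, baseline adherence and randomisation stratum; or
- a logistic regression at one prespecified visit, adjusted for baseline adherence and stratum.

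State which arm contrast is primary and report it with a 95% confidence interval. If several visits enter one model, account for the correlation within patients. Say which outcome each listed regression serves. Keep Cochran's Q, spelled out as such, for describing change within each arm. Reword the expectation in section 4 as a difference between arms.

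The cost is one rewritten paragraph and one sentence. The data are already scheduled for collection, the SPSS version named in section 3.12 offers these models, and section 4 says that recruitment was not complete at the time of writing.
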